## Abstract

The Dutch population is rapidly ageing, and a growing number of people are suffering from age-related health problems such as obesity, cardiovascular diseases and diabetes. These diseases can be prevented or delayed by adapting healthy behaviours. However, making long-lasting lifestyle changes has proven to be challenging and most individual-based lifestyle interventions have not been effective on the long-term. Prevention programs focused on lifestyle should involve the physical and social context of individuals, because the (social) environment plays a large role in both conscious and unconscious lifestyle choices. Collective prevention programmes are promising strategies to mobilize the potential of the (social) environment. However, little is known about how such collective prevention programs could work in practice. Together with community care organization Buurtzorg, we have started a 5 year evaluation project to study how collective prevention can be practised in communities. In this paper, we discuss the potential of collective prevention and explain the methods and goals of our study.

## 1. Introduction

The world’s population is rapidly ageing, resulting in a growing number of people with a multitude of health problems related to older age [1], such as cardiovascular diseases, diabetes and obesity. Social and psychological aspects such as loneliness and stress are also common among older people and may negatively impact a person’s health and quality of life. Current healthcare systems, which are mainly focused on curative care and acute conditions, are struggling to provide the necessary care for ageing populations [1]. In order to improve the lives of older people and build stronger, healthier societies, The World Health Organization (WHO) has declared 2020–2030 the Decade of Healthy Ageing. Healthy ageing is defined as “the process of developing and maintaining the functional ability that enables well-being in older age” [1]. Functional ability relates to the interactions between people and their environment. Both social and physical environments influence people’s abilities to do the things that are important to them and can improve the quality of life. The action plan for the Decade Of Healthy Ageing requires a society-wide response and emphasizes the need for collaboration with older people, engaging them in the community and create age-friendly, physical, social and economic environments [2].

The above-described paradigm of healthy ageing requires public health policies that focus on preventive care and multidimensional integrated healthcare services instead of the fragmented healthcare designed to cure acute diseases [3]. Beard and colleagues highlight the importance of the shared responsibility of long-term care with families and communities, and of removing barriers to social participation. Such public health policies can find inspiration from countries such as Cuba and Japan where population-wide preventive care has been implemented and the health benefits of a more collective, preventive approach have become evident [4,5]. Cuba, for instance, is a middle-income country with limited resources available for healthcare. At the same time, the life expectancy at birth is almost equal to that of high-income countries. This is considered to be primarily the result of their community-based healthcare approach. The Cuban healthcare system is designed to prevent health problems by focusing on primary care and health promotion in the community [6]. This is illustrated by *Círculos de Abuelos*, a successful long-standing population wide program to promote social and physical activities in older adults [7,8]. The program was founded in 1987 and in 2018 almost 40% of Cuba’s older population participated in the program [9,10]. Other countries such as Venezuela, Panama and Colombia have also started implementing this program. Another example comes from Japan, where the government switched their long-term care prevention from a strategy focused on high-risk individuals to a community-based strategy by organizing ‘salons’: social participation interventions during which older people can gather for enjoyable and educational programs [5]. Participation in these salons was associated with a decrease in cognitive decline and long-term care needs. The Japanese government has also funded Silver Human Resource Centres (SHRC), created by local communities and municipalities, that provide part-time work for people after retirement [11]. These well-established Centres are meant to improve the role and status of older people and help them improve or maintain social participation in the community. The majority of SHRC members are men, for whom working at a SHRC job is associated with increased well-being [12]. This effect was not found for women, possibly due to the fact that more women than men joined for financial reasons. The general motivation for joining a SHRC was psychological growth.

The Netherlands is also taking steps towards a healthier population by focusing more on prevention, as described in the 2018 National Prevention Agreement. This agreement outlines goals for reducing smoking, overweight and excessive alcohol consumption through a healthier lifestyle and changes in the environment such as smoke-free areas, regulations for fewer calories in food, and restrictions on marketing of alcoholic drinks [13]. Building on the goals of this agreement and taking inspiration from the previously mentioned examples from other countries, community healthcare organisation Buurtzorg has taken up the initiative to find new ways of implementing prevention strategies and evaluating its effects on the population in order to contribute to a better healthcare system for the ageing population in the Netherlands. Buurtzorg is a pioneering community care organisation with a nurse-led model of holistic care with self-managing teams of nurses [14]. The nurses help their clients to explore the possibilities to engage their environment and social network in working towards independence and improved quality of life. Buurtzorg’s vision on community healthcare aligns with the WHO healthy ageing framework and with the idea that collective prevention strategies should focus on all the aspects that influence health and well-being, from physical functioning to social environment.

While collective community-based strategies to prevent non-communicable diseases have a large potential, successful implementation in a local context remains difficult in most developed countries [15,16,17]. The diversity in context, design, measurement and evaluation makes it difficult to identify effective community-wide prevention strategies. We need more evidence on and guidelines for effective collective prevention programmes that suit the needs and wishes of the communities and that take the physical and social environment into account. Moreover, we need to further investigate indications for the long-term effects of these programmes on health and well-being of participants. In this article, we describe the study protocol of a Dutch nationwide experiment, developed together with Buurtzorg, with collective prevention strategies in local contexts.

### Background

Lifestyle changes such as adopting a healthy (Mediterranean-type) diet and more physical exercise can prevent or improve many age-related health problems [18]. For cardiovascular diseases, for example, over 70% of the cases and deaths in a worldwide population were attributed to modifiable risk factors, which mainly consisted of metabolic and behavioural risk factors [19]. Type 2 diabetes is another common disease that is related to lifestyle. People with a high adherence to a healthy lifestyle (healthy diet, physical activity, no smoking, weight loss and alcohol-intake) have a 78% less likely to develop type 2 diabetes then people with low or no adherence to healthy lifestyle [20]. Furthermore, up to 40% of dementia cases can be prevented or delayed through a healthy lifestyle [21]. In addition to the earlier mentioned well-known lifestyle factors, social and cognitive factors such as social support, leisure and education also play an important role.

Changing one’s lifestyle is challenging, as there are usually no immediate health rewards. Nonetheless, most preventive lifestyle interventions are targeted at the individual and are not part of regular health care [22,23,24]. While these lifestyle interventions, such as counselling, education, physical training, and cooking workshops may be organized in groups, the responsibility is put on the individual to eat healthily, exercise often, obtain enough rest and maintain other healthy habits in an environment and society that does not promote these healthy behaviours [24,25]. These individual-focused lifestyle programmes have shown to be effective in improving risk factors such as physical activity and bodyweight, but the effectiveness of these interventions is often short-lived and declines with longer follow-up [15,26]. Community engagement has been identified as a key component for maintaining the effects after the end of the intervention [15]. This could be partially explained by the notion that a person’s surroundings and norms and values of people around them have a strong influence on their lifestyle and their ability to change this lifestyle [27,28]. Therefore, it may be more effective to address lifestyle through a collective community-based approach, rather than an individual approach. Within a collective community-based approach, the whole community assumes ownership over a health problem and takes action to address it [29]. Healthy behaviour is best maintained when it fits in people’s daily routine and when it can be combined with something pleasant, such as social relations or activities [27,28]. Individuals with obesity for example can only maintain their weight loss on the long term if they are in an environment that promotes healthy eating and physical activity [24,30,31]. These studies indicate that the social environment is an important factor in health promotion and adherence to a healthy lifestyle.

Many studies indicate the potential of public prevention, but there is still a lack of knowledge about the effective elements of collective prevention in practice and the long-term effects on health and well-being measures [32,33,34]. One important element for collective prevention is investment in community capacity building, as this will lead to more and sustained positive health outcomes [15]. However, as Nickel and Von dem Knesebeck mention [34], in a community there is usually a minority of more active and participative individuals who provide input on the needs and interests of community members, while too little is known about the silent majority. This may lead to over-representation of certain interests, making it difficult to create a program that is supported by all community members. This can affect the effectiveness and sustainability of a collective prevention program.

Collective prevention strategies can take place in collaboration with health care professionals (e.g., general practitioners, physiotherapists, dieticians and district nurses). Especially district nurses (DN) in the Dutch system are familiar with the local context and generally trusted by community members, as they work in close contact with and in the personal environment of their clients. In the Netherlands, district nurses provide care assistance at home. In general, they provide nursing and personal care (e.g., assisting with activities of daily living (ADL), wound care and medication). Their medical expertise and status may contribute to the approachability and willingness of community members to work on a collective prevention project together. Even though there are several collective prevention initiatives in the Netherlands, (e.g., Social Connector [35] as linkage between care, well-being and active citizenship and Community Wise [36] where older members of low SES neighbourhoods took part in 12 active meetings focused on healthy lifestyle) only few can be found to have involved DN [35,36]. An exception is Positive Health in Vensterpolder, where a community care organisation was a stakeholder, but did not have a large role in the project [37]. However, this project turned out to be too much focused on the individual rather than the collective, according to the project leader. There is evidence for nurses having a key guiding or coaching role in lifestyle intervention programmes [38,39].

Thus far, collective prevention initiatives have not often been well documented and studied with validated methods. Furthermore, much research on this subject consists of randomized controlled trials, that are likely too short or not intensive enough to measure change in outcome measures such as participation and quality of life [40,41]. Action research may complement these studies, as community members are involved in the collective prevention project from the start. This may lead to community engagement and projects that are adapted to the local context. In the next section we describe the protocol of our “Collective Prevention” study in which we will evaluate several collective prevention ‘projects’—interventions or activities focused on a healthy lifestyle, social participation, and well-being—designed by DN and community members in their neighbourhoods according to the needs of the community. We will study the effective elements and required motivations and skills from DN for successful collective prevention projects and evaluate the health and social effects of these projects on the community members and the effects on work satisfaction for DN.

## 2. Materials and Methods

### 2.1. Population

The study population in this Collective Prevention project will consist of two groups: DN and community members. The DN are all employees of community healthcare organisation Buurtzorg. Buurtzorg has created a model of care in which self-managing teams of 6–12 nurses deliver all the care that a patient needs. They help people get ready in the morning, wash them, give medication, but also provide medical care such as wound treatment. The teams try to involve the formal and informal networks of their patients to sustain independency for as long as possible. The teams organize their work together and share the workload and responsibility for the quality of care. Buurtzorg has invited all interested teams to apply for the current project by submitting their motivations to work on prevention in their work area. The whole team needs to be on board with the project and they are made aware that they will spend roughly 8 hours a week on the project. The motivations and capabilities of the teams were assessed during an interview. At the time of writing, 18 Buurtzorg teams, from 14 different localities all over the country, are selected to participate. These localities vary in number of inhabitants (1230–19,400), mean income (€26,000–€40,000) and urbanity (1–5) on a scale from 1 (most urban: >2500 addresses per km^2^) to 5 (least urban: <500 addresses per km^2^) [42]. The target population of the collective prevention projects consists of the 55+ population in the neighbourhoods under study. The only strict inclusion criterium for this study is that the participants live in one of the neighbourhoods under study and participate in the project in the neighbourhood on a regular basis. DN will be responsible for recruitment of this study population through interviews and networking in their locality, for which they will receive training and tips during workshops led by the researchers. Participation in both the prevention project and this study is voluntary and, therefore, we work with a convenience sample. Given the range of localities we aim for a diverse population in terms of sex, civil status and income. We expect to involve approximately 25–30 community members per site, amounting to a total of 350–420 individuals in our community sample.

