The study will consist of three phases. First, DN of each team will create an overview of their neighbourhood based on their prior knowledge, publicly available data, observations about the physical and social environment, networking with stakeholders and qualitative data gathered through interviews with community members. This overview will provide direction for possible health-related risks or issues in the neighbourhood that might be addressed in a local collective prevention project. In the second phase is the DN will, together with community members, prioritize and decide which subject to focus on. The third phase consists of designing and organising a collective prevention project in the locality together. The collaboration with community members in these steps is key to ensure that the programme is relevant to and created with the community, which are important preconditions for community building.

The time investment for the project as a whole, as well as the possible difficulties or delays in any of the phases will differ between the teams. Therefore, we use a stepped wedge design in this project. We will follow the teams and their prevention projects for 4–5 years, at the end of which we will be able to understand how collective prevention projects can be developed in collaboration with DN and community members, what the effective elements and obstacles are, and how it affects public health. The multimethod design ensures a rich and diverse representation of the impact of the collective prevention projects on the target audience. The quantitative effect measures will provide an indication of the change over time and possibly between groups. The qualitative measures in this study will provide a more detailed and personal image of health, well-being, motivations and other experiences during the project, as well as insight into elements that matter in the process. This will help to determine which projects can be considered successful and how they might be implemented on a larger scale.

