In the first phase, the DN will gather information about people’s social situation and common health issues in the neighbourhood where they work by conducting at least 30 interviews with community members and health professionals such as general practitioners, physiotherapists and dietitians. DN will receive instructions and training for conducting interviews during webinars and workshops. The goal of these interviews is to determine what community members of every participating neighbourhood consider important aspects of public health in their lives and environment that may be improved by a prevention project. During this phase, the Buurtzorg teams will also ask permission and gather contact information from community members (and other stakeholders) who are willing to participate in this study. The researcher or co-researcher will explain the purpose, procedure, potential benefits and risks of participating in this study orally and in writing. We will also gather statistics about health problems and other relevant factors in the neighbourhood via publicly available data (such as the National Institute for Public Health and the Environment (RIVM) or Statistics Netherlands (CBS)). Based on this analysis, Buurtzorg teams together with community members will identify the topic for their prevention programme and develop a plan of action by again conducting (group) interviews and using design methods that will be discussed during monthly webinars.

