#### 2.4.1. Community Members

##### Health and Well-Being

Health and well-being of the community members will be evaluated by measuring two variables—quality of life and experienced health—annually in each project. Quality of Life will be measured using the validated Dutch ICECAP-O, the ICEpop CAPability measure for Older people, that consists of 5 items on a 4-point scale [43,44]. We use this measure that is specifically developed for older adults, because we expect that the majority of our study population will be older adults. Moreover, we expect that a capability approach, mapping both the capabilities in the environment as well as the degree to which members can take up these capabilities fit with the environmental approach of collective prevention. Experienced Health will be measured with the 4-item index of Perceived Physical Health [45]. These items are scored on a 5-point scale. The questions of this measure were translated from English to Dutch for the current project. We will use the WHO methodology for translation and adaptation of instruments to translate this instrument. In this methodology, we will translate and backtranslate the instrument after which we will pilot test it before using it for data collection in the whole study [46].

In the last year of the study, we will interview community members who participate in the prevention projects to gather qualitative data about health and social effects, their experience with the prevention projects and how it may impact their daily life. We will pose questions such as “What does preventive care mean for you?”, “How has the prevention project impacted your physical functioning, condition or energy level?”, and “What changes have you experienced in your social life or network since participating in this project?” (see Supplementary Materials, Topic list S1). Additional data about community members’ experiences in this project may come from (participatory) observation sessions throughout the 4 years of this study.

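### Eligibility rests on regular participation in a local project that is designed only after people have been approached, so selection on attendance can bias the uncontrolled change estimate

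*Protocol article*

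**What the plan says.** Section 2.1 (Population) gives one binding entry rule. "The only strict inclusion criterium for this study is that" "participants live in one of the neighbourhoods under study and participate in the project in the neighbourhood on a regular basis". It neither defines regular nor says when it is assessed. The same section sets a wider target, "The target population of the collective prevention projects consists of the 55+ population in the neighbourhoods under study", and describes the sampling plainly: "Participation in both the prevention project and this study is voluntary and, therefore, we work with a convenience sample".

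The timing is spread over two sections. In section 2.2 (Design) the local project comes last: "The third phase consists of designing and organising a collective prevention project in the locality together". In section 2.3 (Procedure) recruitment for the study comes in the first phase, when "the Buurtzorg teams will also ask permission and gather contact information from community members (and other stakeholders) who are willing to participate in this study". Section 2.3 also places baseline at the start of the project, with annual repeats and four measurement times in all.

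Section 2.4.1 (Health and Well-Being) describes the closing interviews on effects: "In the last year of the study, we will interview community members who participate in the prevention projects". Section 2.6.1 analyses change within subjects over the four time points by repeated measures MANOVA. Section 3.2 (Limitations) confirms that there is no control group.

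**The concern.** Whether someone takes part regularly can be seen only over time, once there is something to attend. An entry condition of that kind selects on an event after exposure. Perceived health, quality of life and social participation are the outcomes, and they could well influence whether an older person keeps coming. If people whose health or social life declines attend less and so fail the criterion, average change among those counted looks better than change among everyone who started.

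A comparison group selected in the same way might cancel part of this, but there is none for community members. The selection therefore passes straight into the within-subject estimate for primary objective 1, the effect on participants' health and well-being. The effect interviews could lean the same way, since no part of the qualitative plan says that people who stopped will be heard.

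**Working it through.** **1. Order of events**

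| Step | Timing | Section |
|---|---|---|
| Permission and contact details | Phase 1 | 2.3 |
| Topic chosen with the community | Phase 2 | 2.2 |
| Local project designed and organised | Phase 3 | 2.2 |
| Baseline questionnaire | Start of the project | 2.3 |
| Regular participation observable | After the start; no time stated | 2.1 |

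The project in the baseline sentence may mean the whole study or the local activity. If it means the whole study, baseline precedes any knowledge of who is regular, and applying section 2.1 then leaves out people who already have a baseline. If it means the local activity, regularity is still unknown on the first day. Either the same exclusion follows later, or people enter once they are regulars and their first measurement is no longer pre-exposure.

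**2. The plan's own figure.** 14 localities × 25 = 350 and 14 × 30 = 420, which reproduces the stated 350–420. The article gives no power, effect size, SD or stopping rate for community members.

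**3. Size of the bias when non-regulars are left out (illustration).** Let a fraction f of those enrolled stop, with mean change d SD worse than that of the stayers. If stayers change by m, the whole cohort changes by (1 − f)m + f(m − d) = m − f·d. Stayers overstate change by f·d.

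- f = 0.2, d = 0.2: 0.04 SD
- f = 0.2, d = 0.4: 0.08 SD
- f = 0.4, d = 0.2: 0.08 SD
- f = 0.4, d = 0.4: 0.16 SD
- d = 0: no bias at any f

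Both f and d are assumptions. The formula does not cover enrolment of regulars with a late baseline. There, change before the first measurement is simply lost.

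**4. Detectable change among those who remain.** For one later wave against baseline, with 80% power and two-sided 5%, the detectable change is 2.8 × √(2(1 − r)) / √n in SD of the score. Here r is the repeat correlation, assumed 0.5–0.7, and people are treated as independent. The n must be the stayers: 350 × 0.6 = 210 up to 420 × 0.8 = 336.

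- n = 336, r = 0.7: 2.8 × 0.775 / 18.33 = 0.118 SD
- n = 210, r = 0.5: 2.8 × 1 / 14.49 = 0.193 SD

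**5. Comparison at matching f.**

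- f = 0.4 (n = 210–252): detectable change runs from 2.8 × 0.775 / √252 = 0.137 to 0.193 SD. The bias of 0.16 SD at d = 0.4 falls inside that range; the 0.08 SD at d = 0.2 falls below it.
- f = 0.2 (n = 280–336): detectable change runs from 0.118 to 2.8 / √280 = 0.167 SD. The bias of 0.04–0.08 SD lies below it.

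Only the most adverse assumed corner reaches the detectable change. A smaller bias still matters: at n = 280 and r = 0.5 the standard error is 1 / √280 = 0.060 SD, so 0.08 SD shifts the estimate by 1.3 standard errors.

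**The case against.** Several points on the other side are sound.

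- *Participation may begin with planning.* Community members help to choose the topic and design the project, so some participation is visible before activities run. This stands in part, but regular participation would still be recognised only afterwards, and the article leaves it undefined.
- *Nothing says that leavers are dropped.* Section 2.1 is an entry rule. A reader might infer that anyone who later stops is removed or no longer sent the questionnaire. The article does not say so, and follow-up after stopping may be set out in the full protocol. What stands is narrower: the rule as printed excludes people who do not become regulars.
- *The qualitative data are wider than the last-year interviews.* A reader might infer that effects are explored only in the last year, only with people still attending, and so with those who liked the project. The documents do not support that. Section 2.3 has interviews and focus groups during the four years, and section 2.4.1 adds observations throughout. The interview sentence contains neither only nor still, and nothing is said about why people stay. It remains true that no component is stated to include people who stopped.
- *Question wording.* Of the three sample questions in section 2.4.1, one is neutral and two presuppose an effect. The full topic list is not shown, so no judgement on the whole list is possible.
- *The introduction's silent majority.* This might be read as a warning about attrition. It concerns whose needs and interests shape a programme, and does not bear on this point.
- *The limits are partly disclosed.* The article admits a convenience sample, self-selected nurse teams and no control group, promises only an indication of change over time, and frames objective 1 around participants. That moderates the claims. It does not disclose selection of community members by attendance, which affects the change estimate itself as well as its generalisability.

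**Conclusion.** The point holds as a fault in a rule that this article itself fixes. Regular participation is part of the sole strict entry criterion, no time of assessment is given, and consent and baseline come before it can be known. With a within-subject analysis and no control group, nothing later in the design corrects the resulting selection.

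The likely direction is upward. That rests on the unproven but plausible premise that people who do worse attend less. The documents do not determine the size. On the assumptions shown it is 0.04–0.16 SD, against a detectable change of about 0.12–0.19 SD among those who remain, and it vanishes if stopping is unrelated to change. Clustering within the 14 localities is ignored in the detectable change and would probably enlarge it. The case for change does not depend on these figures: a pre-exposure baseline that was not taken cannot be recovered later.

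**What to change.** 1. Replace the criterion in section 2.1 with residence in a study neighbourhood plus consent, given in phase 1 or at first attendance, with the baseline questionnaire completed at or before that point.
2. Send the annual questionnaire to everyone in that cohort, whether or not they still attend.
3. Record attendance each year and use it in a secondary analysis, not as a condition of entry.
4. Within the planned number of final interviews, reserve a fixed share for people who stopped. Reword the two leading sample questions in section 2.4.1 so that no change is an equally easy answer.
5. If the present criterion is kept, define regular, state when it is judged relative to baseline, and limit conclusions to regular participants. This narrows the claim but does not restore a missing pre-exposure baseline.

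The cost is small: revised eligibility and interview-sampling wording, a yearly attendance record, and questionnaires to people whose contact details are largely being collected in phase 1 anyway. The downsides are a probably less favourable estimate and some non-response among those who stop.
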